### ROC Analysis of Binary Outcomes

A ROC analysis will be performed to investigate the ability of the investigational biomarkers to predict each of the binary outcome variables (i.e. whether the subject recovered [category 1 or 2] from DILI or not). Estimates of the Area Under the ROC Curve (AUROC) with 95% confidence interval (CI) will be produced. Further details for the analysis will be specified in the statistical analysis plan.

AUROCs with 95% confidence interval will also be produced for the standard biomarkers (ALT, total bilirubin and ALP) and the commercial test - ActiTest.

In addition, AUROCs based on a combination of biomarkers may be investigated if they outperform the standard biomarkers.

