# Objectives

### Primary Objective

The primary objective of this study is to validate the performance of the new investigational biomarkers (or a combination of biomarkers) measured at baseline (or from baseline to W12) in its prediction of outcome. The outcome type that is considered of primary importance is whether after admittance with DILI, the patient will reach full recovery at W12.

These new biomarkers will be compared to ALT and total bilirubin, which are the "Standard of Diagnosis", by analogy with the "Standard of Care" for treatment.

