### Endpoints

### Primary Endpoint: Binary Recovery Outcome

The primary endpoint is the category 1 recovery outcome (see Section 1.6.1), that is the "full" recovery at the last visit (W12).

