### Secondary Endpoints: Categorical Recovery Outcome

The recovery outcome with 3 ordered categories [1] full recovery, [2] partial recovery including adaptive response and [3] not recovered including severe complications **(see Section 1.6.1)** will be defined as a secondary outcome with normal ranges used as defined in Section 1.7.4.

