### Biomarker Thresholds

The criterion to define biomarker thresholds will be clarified in the SAP, e.g. based on the threshold that minimizes the distance to the top left corner of the ROC.

Cross-validation will be used to quantify the sensitivity and specificity of the thresholds. Thresholds will be used to classify subjects in recovery outcome as full/ partial or no recovery (or types of DILI) and the sensitivity and specificity calculated based on the outcome at W12.

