### Categorical Outcome

A ROC analysis with a categorical outcome will be performed to investigate the ability of the investigational biomarkers to distinguish between each pairwise set of outcome categories. The Obuchowski Measure (a weighted average of AUROCs across the pairwise categories) will be used to summarize the performance of each investigational biomarker [8].

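### Section 7.1 describes the binary recovery outcome as categories 1+2 versus 3, which contradicts the primary endpoint (category 1 versus 2+3) and matches no endpoint in Section 6; Section 7.2 does not settle the cut

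*Protocol*

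**What the plan says.** Section 1.6.1 (Recovery Outcome) sorts patients at week 12 into full recovery [1], partial recovery [2] and no recovery [3].

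The primary outcome is stated twice, consistently. Section 2.1 (Primary Objective) asks whether "the patient will reach full recovery at W12". Section 6.1 (Primary Endpoint: Binary Recovery Outcome) says "The primary endpoint is the category 1 recovery outcome".

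Section 7.1 (ROC Analysis of Binary Outcomes) says that the ROC analysis serves "to predict each of the binary outcome variables" and then explains this in a parenthesis opened by i.e.: "whether the subject recovered [category 1 or 2] from DILI or not". Further ROC detail is left to the SAP.

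Section 7.2 (Biomarker Thresholds) says: "Thresholds will be used to classify subjects in recovery outcome as full/ partial or no recovery".

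The three-category outcome is a separate, secondary endpoint in Section 6.2. Section 7.3 analyses it by the ability of each biomarker "to distinguish between each pairwise set of outcome categories".

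**The concern.** A binary recovery outcome needs one cut through the three ordered categories. Sections 2.1 and 6.1 put it between 1 and 2. The parenthesis in Section 7.1 puts it between 2 and 3. A partial-recovery patient is therefore a failure under the endpoint and a success under the analysis text.

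The study exists to show whether new biomarkers predict outcome better than ALT and total bilirubin, and Sections 1.6.3 and 7 select biomarkers and combinations by cross-validation on all the data. The outcome definition decides which AUROC is estimated, where the threshold falls, what its sensitivity and specificity are, and possibly which biomarkers are selected. If the Section 7.1 split is used, these results describe prediction of non-recovery (category 3 alone), not of failure to reach full recovery.

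**Working it through.** **Step 1: set the definitions side by side.**

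| Place in protocol | Recovered | Not recovered |
| --- | --- | --- |
| 2.1 Primary Objective | 1 | 2, 3 |
| 6.1 Primary Endpoint | 1 | 2, 3 |
| 7.1 ROC Analysis (parenthesis) | 1, 2 | 3 |
| 7.2 Biomarker Thresholds | unclear | unclear |

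**Step 2: could Section 7.1 be describing some other endpoint?** Section 6.2 has three ordered categories and no cut. Section 6.3 has severe biochemical DILI, severe clinical DILI and type of injury. Section 6.4 times full recovery, severe biochemical DILI and severe clinical DILI. None of these is 1+2 versus 3, so the parenthesis matches no defined endpoint.

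**Step 3: does Section 7.2 settle it?** Its phrase allows three readings: full or partial versus none (1+2 versus 3), full versus partial or none (1 versus 2+3), or three classes. The second agrees with Section 6.1 and the first with Section 7.1. The text does not decide between them.

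**Step 4: does Section 7.3 supply the missing contrast?** No. Its AUROCs are pairwise (1 v 2, 1 v 3, 2 v 3) and are combined with weights for the secondary categorical outcome. None of them is 1 versus 2+3.

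**Step 5: illustrate the size.** The only input from the protocol is N = 500 (Section 3.1). It comes with no category shares, target AUROC or precision goal, so there is no protocol figure to reproduce. Everything else here is assumed: shares p1/p2/p3 and AUROC A = 0.75 under both splits.

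Non-recoveries are N(p2 + p3) under Section 6.1 and N·p3 under Section 7.1. The number of patients classed differently is N·p2.

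Hanley-McNeil variance, with n1 non-recoveries and n0 = N − n1:

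var = [A(1−A) + (n1−1)(Q1−A²) + (n0−1)(Q2−A²)] / (n1·n0), where Q1 = A/(2−A) and Q2 = 2A²/(1+A).

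At A = 0.75: A(1−A) = 0.1875, Q1 = 0.6000, Q2 = 0.6429, A² = 0.5625, so Q1−A² = 0.0375 and Q2−A² = 0.08036.

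With shares 70/20/10%:
- Section 6.1 cut, n1 = 150, n0 = 350: (0.1875 + 149×0.0375 + 349×0.08036)/52,500 = 33.82/52,500 = 0.000644. SE = 0.0254, and 1.96×SE = 0.050.
- Section 7.1 cut, n1 = 50, n0 = 450: (0.1875 + 49×0.0375 + 449×0.08036)/22,500 = 38.11/22,500 = 0.001694. SE = 0.0412, and 1.96×SE = 0.081.

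| Assumed shares 1/2/3 | Classed differently | Non-recoveries, 6.1 / 7.1 | 95% half-width, 6.1 / 7.1 |
| --- | --- | --- | --- |
| 60/25/15% | 125 | 200 / 75 | 0.045 / 0.067 |
| 70/20/10% | 100 | 150 / 50 | 0.050 / 0.081 |
| 80/15/5% | 75 | 100 / 25 | 0.059 / 0.113 |

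**Step 6: the AUROC itself moves.** Take a normally distributed marker with SD 1 and assumed means 0, m2 and 1.2 in categories 1, 2 and 3, with shares 70/20/10%. For two categories whose means differ by d, AUROC = Φ(d/√2). Then:
- 1 versus 2+3: [0.2·Φ(m2/√2) + 0.1·Φ(1.2/√2)]/0.3
- 1+2 versus 3: [0.7·Φ(1.2/√2) + 0.2·Φ((1.2−m2)/√2)]/0.9

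| m2 | 1 v 2+3 | 1+2 v 3 |
| --- | --- | --- |
| 0.3 | 0.66 | 0.79 |
| 0.6 | 0.71 | 0.77 |
| 1.0 | 0.77 | 0.75 |

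The marker with m2 = 0.3 scores lowest of the three under the primary endpoint and highest under the Section 7.1 split. The choice of cut can therefore reverse a ranking of biomarkers.

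**The case against.** The best defence is that Section 7.1 covers all the binary outcomes and Section 6.1 carries the heading Binary Recovery Outcome, so the primary endpoint is nominally within scope. The parenthesis cannot be an exhaustive definition either: read literally, it would also drop severe biochemical DILI, severe clinical DILI and type of injury. On this view it is a careless gloss, and the SAP, which is not at hand, may use the correct cut.

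Much of this stands, and it limits the point. Three stronger readings are tempting and are not supported.

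- A reader might infer that the primary endpoint is not analysed at all. The text does not go that far, because the scope of Section 7.1 nominally includes it and no analysis in Section 7 is labelled primary.
- A reader might take Section 7.2 as a second instance of the 1+2 versus 3 split. Its wording is equally compatible with full versus partial or none.
- A reader might infer that two primary analyses are left open for a choice after results are seen. That depends on what the SAP says. The protocol itself names one primary outcome clearly.

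The defence does not remove the contradiction. The bracket gives category numbers, so it is more than loose use of the word recovered. Leaving further detail to the SAP does not cover a dichotomy that the protocol has already written down: an SAP author must depart from either Section 6.1 or Section 7.1. The analyses of pairwise categories and of time to full recovery do separate full from partial recovery, but they are secondary and do not estimate 1 versus 2+3.

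**Conclusion.** The point holds as a contradiction within the protocol. The only recovery dichotomy spelled out in the ROC section differs from the primary endpoint by the whole of category 2 and corresponds to no endpoint in Section 6. The threshold section is ambiguous and does not resolve it. This part rests on the text alone and needs no assumption.

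The size of the effect is unknown. Category 3 is contained in categories 2+3, so the Section 7.1 outcome cannot be the more common one, but how much rarer it is depends on shares that the protocol does not give. Over the assumed shares the 95% half-width grows by a factor of about 1.5 to 1.9 (0.067/0.045 to 0.113/0.059). That comparison holds AUROC at 0.75 for both splits, which is itself an assumption. Lost precision is the side effect. The main consequence is that a different outcome is predicted, with an AUROC that may be higher or lower.

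Because this concerns the definition of the primary outcome, it should be corrected before any biomarker result is analysed.

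**What to change.** - **Section 7.1:** replace the parenthesis with a statement that the ROC analysis of the primary endpoint compares category 1 with categories 2 and 3 combined, and refer to Section 6.3 for the other binary outcomes.
- **Section 7.2:** state that the primary thresholds, with their sensitivity and specificity, use that same cut.
- **Section 6.3:** if 1+2 versus 3 is of interest, list it as a named secondary binary endpoint. Otherwise leave it out.
- **SAP:** check that its primary ROC analysis, thresholds and biomarker selection use the Section 6.1 cut.

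The cost is a few sentences in a protocol amendment. The three categories are already derived from planned measurements, so no visit, sample or data item changes.

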### Biomarker Thresholds

The criterion to define biomarker thresholds will be clarified in the SAP, e.g. based on the threshold that minimizes the distance to the top left corner of the ROC.

Cross-validation will be used to quantify the sensitivity and specificity of the thresholds. Thresholds will be used to classify subjects in recovery outcome as full/ partial or no recovery (or types of DILI) and the sensitivity and specificity calculated based on the outcome at W12.

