### Secondary Objectives

The new biomarkers will be compared to ALT and total bilirubin, which are the "Standard of Diagnosis" (including Hy's Law), and to ActiTest which is already commercially available for the secondary objectives:

- - - Investigate the performance of investigational biomarkers from baseline D0 to Week 12) to predict:

1. A subsequent increase in total serum bilirubin of at least 10 umol/l more than the baseline value (D0) or an elevation of total bilirubin to 34 umol/l (Hy's law is TBILI 2xULN together with ALT 3xULN) at any other measurements between D1 to W12;
2. Death or severe liver complications (including transplant and complications associated with liver failure such as: hepatic encephalopathy, hemorrhage, associated liver failure complications: kidney failure, medical ventilation, circulatory dysfunction and infections.
3. Type of liver injury (hepatic, cholestatic and mixed).
4. Time to discharge from hospital.
   - - For each of the outcomes in (i) to (iii) determine the best investigational biomarker with associated thresholds.
     - For each of the outcomes in (i) to (iii) determine the best combination of biomarkers with associated threshold.
     - Type of drugs suspected in DILI will be assessed.
     - The prevalence of associated liver risk factors such as alcohol consumption, metabolic factors, history of familial liver disease, history of drug adverse events, history of recreational drugs (cocaine, ecstasy, amphetamines), combination of different drugs and herbals will be assessed and may be incorporated into statistical models.

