### Severe Biochemical DILI

A patient will be deemed to have “severe biochemical DILI” if the patient has:

- An increase in total serum bilirubin of at least 10 umol/l more than the baseline value (D0); or
- An elevation of total bilirubin to 34 umol/l (Hy's law) at any other measurements between D1 to W12;

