### Severe Clinical DILI

- Dies of any cause
- Requires a transplant
- Complications associated with liver complications/failure such as: hepatic encephalopathy, hemorrhage, kidney failure, medical ventilation, circulatory dysfunction and infections.

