# Statistical Methods

Statistical methods will be described in full in a statistical analysis plan (SAP).

Biomarkers and combinations of biomarkers will be assessed and selected using cross-validation on all of the data in the study.

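### Section 7.2 fixes the W12 outcome as the only reference for threshold sensitivity and specificity; that fits recovery but not injury type or severe biochemical DILI, for which Section 2.2 also requires thresholds.

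*Protocol*

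**What the plan says.** Section 2.2 (Secondary Objectives) lists three outcomes that need thresholds: (i) a bilirubin rise or elevation, (ii) death or severe liver complications, and (iii) type of liver injury. The instruction is "For each of the outcomes in (i) to (iii) determine the best investigational biomarker with associated thresholds", and it is repeated for combinations of biomarkers.

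Section 7.2 (Biomarker Thresholds) makes three statements:
- On how a cut-off is chosen: "The criterion to define biomarker thresholds will be clarified in the SAP".
- On accuracy in general: "Cross-validation will be used to quantify the sensitivity and specificity of the thresholds".
- On what is classified and against what: thresholds sort subjects into full/partial or no recovery ("or types of DILI) and the sensitivity and specificity calculated based on the outcome at W12").

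The endpoint definitions are:
- Recovery (Sections 1.6.1 and 6.1): classified at the end of the 12-week follow-up.
- Severe biochemical DILI (Section 6.3.1): a rise of at least 10 umol/l over D0, or "An elevation of total bilirubin to 34 umol/l (Hy's law) at any other measurements between D1 to W12".
- Severe clinical DILI (Section 6.3.2): begins with "Dies of any cause", then lists transplant and liver-related complications. No time window is given. Section 6.4 counts time to this event from D0.
- Type of injury (Section 6.3.3): each type's indicator is set to present when that type occurs at a subset of time points.

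**The concern.** A threshold's sensitivity and specificity mean something only against a stated reference outcome. Section 7.2 states one reference, and it is a status at a single visit. Two of the outcomes for which thresholds are an explicit objective are defined over the whole follow-up, and one of these, injury type, is named in 7.2 next to the W12 reference.

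If the W12 reference were applied to these outcomes, a marker that correctly flagged an early bilirubin peak would be charged with a false positive whenever the patient had recovered by week 12. Injury type would be judged from enzyme ratios taken after the injury had subsided. The choice of best biomarker and cut-off for these outcomes could then rest on the wrong labels.

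**Working it through.** The point is textual. The protocol states no accuracy, event rate or power figure here, so there is no plan figure to reproduce. The check sets the W12 reference against each endpoint in turn.

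**Recovery.** Defined at W12, so the reference matches.

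**Severe biochemical DILI.**
- Section 1.7.4 sets the upper limit for total bilirubin at 17 umol/l, so 2 x ULN = 2 x 17 = 34 umol/l. The elevation that makes an event in Section 6.3.1 is therefore also the bilirubin boundary of full recovery in Section 1.6.1.
- Take a patient with bilirubin 40 umol/l in week 1. At W12 bilirubin is below 34 and no higher than at D0, ALT is below 2 x ULN, and there has been no severe complication.
- This patient is an event, because the elevation counts "at any other measurements between D1 to W12". The same patient is a full recovery at W12. One label cannot stand in for the other.

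**Type of injury.** Section 3.6.1 defines R = (ALT/ULN)/(ALP/ULN), with R > 5 hepatocellular and R < 2 cholestatic. Example with assumed values:
- D0: ALT 20 x ULN, ALP 1.5 x ULN. R = 20/1.5 = 13.3, hepatocellular.
- W12: ALT 1.0 x ULN, ALP 0.9 x ULN. R = 1.0/0.9 = 1.1, cholestatic by the ratio although neither enzyme exceeds its ULN.
- Under Section 6.3.3 the hepatocellular indicator stays present because of the D0 value. A W12 reference would lose it.

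**Severe clinical DILI.** Death and transplant do not reverse by W12, and recovery category 3 includes clinical morbidity and mortality. The mismatch therefore mainly concerns complications that can resolve, such as encephalopathy or infection.

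**Illustration of size (all rates assumed).** Let p be the share of patients with the biochemical event at any visit, and r the share of those events resolved by W12. Let Se = Sp = 0.80 against the any-visit event, with resolution independent of the marker. Scored on W12 status,

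apparent specificity = [(1-p)·Sp + p·r·(1-Se)] / [(1-p) + p·r].

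For p = 0.4 and r = 0.5: (0.6·0.80 + 0.4·0.5·0.20)/(0.6 + 0.2) = 0.52/0.80 = 0.65.

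| p | r = 0.25 | r = 0.50 | r = 0.75 |
|---|---|---|---|
| 0.2 | 0.77 | 0.73 | 0.71 |
| 0.4 | 0.71 | 0.65 | 0.60 |
| 0.6 | 0.64 | 0.54 | 0.48 |

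Sensitivity stays at 0.80 under the independence assumption. The loss falls on specificity.

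**The case against.** The strongest reply is that the W12 phrase belongs to a sentence about recovery, where it is correct, and that nothing in 7.2 says thresholds for outcomes (i) and (ii) are scored on W12 recovery. The preceding sentence promises cross-validated accuracy for thresholds in general. Section 7.1 runs ROC analysis on each binary outcome variable. Section 7 opens with "Statistical methods will be described in full in a statistical analysis plan (SAP". The W12 outcome might also be read as status accumulated by the end of follow-up, when every endpoint is known.

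Much of this stands. A reader might infer that thresholds for severe biochemical and severe clinical DILI get no valid sensitivity or specificity. The protocol does not support that: the general promise in 7.2 covers them, and a SAP that is not shown may specify the reference. A reader might also infer that both severe endpoints run from D1. That window is written only for the biochemical one.

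The objection does not remove the point, for three reasons:
- What 7.2 defers to the SAP is the criterion for choosing a cut-off. The reference outcome is stated in the protocol itself.
- The sentence is not confined to recovery. It also names types of DILI, and there the W12 reference conflicts directly with Section 6.3.3.
- Section 7.1 does not settle the matter. It concerns AUROC, and its parenthesis narrows the binary outcomes to recovered or not.

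The cumulative reading is possible, but the text does not say it.

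**Conclusion.** The point holds as an inconsistency within the protocol. Section 7.2 gives one reference for threshold accuracy. It suits recovery, contradicts the definition of injury type, and does not fit severe biochemical DILI. Outcomes (i) and (ii) need thresholds under Section 2.2 but are not named in 7.2. The consequence is greatest for injury type and the biochemical endpoint, and smaller for severe clinical DILI.

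The size cannot be derived from the documents, which give neither event nor resolution rates. The tabulated specificities show the direction and a possible range under assumed rates and a literal W12 reading; they do not measure an error in the plan. The matter is confined to secondary objectives. The W12 reference for the primary recovery endpoint is sound.

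**What to change.** In Section 7.2, replace the closing reference to the outcome at W12 with: *based on each outcome's own endpoint definition (recovery category at W12; severe biochemical DILI, severe clinical DILI and type of liver injury as defined in the binary endpoints section)*. In the same section, name outcomes (i) to (iii) of Section 2.2 among those whose thresholds are derived and cross-validated.

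The edit should point to the existing definitions and not rewrite them. Fixing injury type at D0 alone would conflict with Section 6.3.3, and starting severe clinical DILI at D1 would conflict with the D0 origin in Section 6.4.

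Cost: a wording change and a few more cross-validated tables. No new data are needed.

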### Categorical Outcome

A ROC analysis with a categorical outcome will be performed to investigate the ability of the investigational biomarkers to distinguish between each pairwise set of outcome categories. The Obuchowski Measure (a weighted average of AUROCs across the pairwise categories) will be used to summarize the performance of each investigational biomarker [8].

### Subgroups and Special Populations

The recovery outcome for each type of DILI (cholestatic, hepatic or mixed) will be investigated separately. The biomarkers that have the highest AUROC estimates will be qualified as good predictors of recovery outcome for the particular type of DILI that is being investigated. Biomarker thresholds will also be calculated for each type of liver injury.

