### Rationale for this Study

In the context of SAFE-T’s DILI qualification program, the aim of this study is to collect blood samples from patients with acute DILI, and to investigate whether a set of innovative biomarkers (see Section 3.6.2) can improve on the performance of standard biomarkers (ALT and total bilirubin) to predict the outcome of DILI.

A pilot study (called "pilot study 3") was initially performed in a predetermined number of 45 patients. The aim was to calculate the number of centers and the time needed to obtain a total sample size of 500 DILI cases for the core protocol 3A (3A for protocol 3 Amended).

The performance of the innovative biomarkers will be compared with the standard biomarkers (ALT and bilirubin).

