### Biomarker Assessment and Selection

Cross-validation using all of the data from the study will be used to assess and select biomarkers and combinations of biomarkers.

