### Patients and Methods

- 1. **Patients**

A total of 500 patients with acute DILI will be included. The duration of follow-up per patient will be 12 weeks.

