### DILI Biomarkers

The SAFE-T DILI team performed a careful and exhaustive review of the current literature and in house data from partners. Approximately 45 potential biomarker candidates were evaluated, using a standard set of criteria. Of the 45 initially evaluated biomarker candidates, 19 biomarkers and 21 components (2 biomarkers combine 2 components: Keratin 18/ccKeratin 18 and paraoxonase 1/Prothrombin) were recommended for clinical qualification. The core set of biomarker candidates to be assessed within the consortium comprises:

| Conjugated/Unconjugated Bile Acids |
| --- |
| Keratin 18 |
| ccKeratin 18 |
| Arginase 1 |
| LECT 2 |
| HPD |
| Regucalcin |
| ST6Gal1 |
| Alpha-1-Fetoprotein |
| GST alpha 1 |
| Osteopontin |
| Paraoxonase 1 |
| MCSF-R |
| Prothrombin |
| miR122 |
| Albumin mRNA |
| Microglobulin precursor mRNA |
| SDH |
| GLDH |
| HMGB1 |
| Hyperacetylated HMGB1 |

In addition to the DILI biomarker candidates listed above, ActiTest used for the clinical diagnosis of chronic necro-inflammatory activity will be also evaluated. ActiTest is a patented biomarker of liver necro-inflammatory histological activity initially validated in patients with chronic hepatitis C and B and with severe obesity. In patients with chronic hepatitis C, ActiTest has higher diagnosis performance than ALT for the diagnosis of the grade of necro-inflammatory histological activity using the METAVIR scoring system as reference. Specificity have been validated in healthy volunteers an in blood donors [4], and is part of the biomarkers assessed in protocol 5.

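### The injury-type rule in Section 7.4 qualifies biomarkers by AUROC rank alone, so it names a good predictor whether or not any marker predicts recovery or improves on ALT and bilirubin

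*Protocol*

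**What the plan says.** Section 7.4 (Subgroups and Special Populations) analyses recovery separately for cholestatic, hepatic and mixed injury and fixes the decision rule: "The biomarkers that have the highest AUROC estimates will be qualified as good predictors of recovery outcome for the particular type of DILI". It does not say how many top-ranked markers qualify, or whether the standard markers stand in the same ranking.

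On the data used, Section 1.6.3 says: "Cross-validation using all of the data from the study will be used to assess and select biomarkers and combinations of biomarkers". The opening of Section 7 repeats that they will be "assessed and selected using cross-validation on all of the data in the study". Neither names a hold-out set or says whether selection is nested.

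Elsewhere the framing is comparative. The primary objective (Section 2.1) is to "validate the performance of the new investigational biomarkers", compared with ALT and total bilirubin, and the rationale (Section 1.6) asks whether the new markers can improve on those two. Section 7.1 provides AUROCs with 95% confidence intervals for new and standard markers and adds that "AUROCs based on a combination of biomarkers may be investigated if they outperform the standard biomarkers". Nothing links these intervals or comparisons to the qualification rule in Section 7.4. Full statistical methods are left to a SAP, which is not shown.

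**The concern.** Ranking is not evidence of performance. One candidate must have the highest estimate in each injury type, so a positive conclusion follows whatever the data show. A marker could be called a good predictor while its true AUROC is 0.5, or while ALT does as well.

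Useless prognostic markers are a realistic possibility. The stage gate (Section 1.6.2) keeps markers associated with established DILI, using healthy volunteers and DILI patients. That is evidence about diagnosis, not about who recovers by week 12.

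The highest of several noisy estimates also overstates the winner's true performance, most of all in small subgroups, which is where this rule applies. At stake is whether a claim of qualification from this study can be relied on.

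**Working it through.** **Inputs from the protocol.** Total sample: "A total of 500 patients with acute DILI will be included". No power or precision inputs accompany that figure; of the pilot study the protocol says "The aim was to calculate the number of centers and the time needed to obtain a total sample size of 500 DILI cases". There is therefore no stated calculation to reproduce. Candidates: "19 biomarkers and 21 components (2 biomarkers combine 2 components: Keratin 18/ccKeratin 18 and paraoxonase 1/Prothrombin) were recommended for clinical qualification". Section 1.6.2 says that only a reduced set will be assayed, so 21 is a ceiling.

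**Assumptions.** 5 or 21 markers assayed; correlation between markers 0.5 or 0; subgroups of 100 (20 in the rarer class) and 150 (30 in the rarer class); each marker's direction fixed in advance; every true AUROC 0.5.

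**Step 1: the rule itself.** With no bar, the probability that some marker is qualified is 1 in each injury type. This follows from the wording and needs no simulation.

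**Step 2: how good the winner looks by chance.** The null standard error of an AUROC is √[(n₁+n₀+1)/(12·n₁·n₀)].
- 100/20: √[101/(12·20·80)] = 0.0725.
- 150/30: √[151/(12·30·120)] = 0.0591.

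Simulated ranges over the assumptions:

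| Subgroup / rarer class | Mean highest AUROC | Chance that it exceeds 0.60 |
|---|---|---|
| 100 / 20 | about 0.56–0.63 | about 27–83% |
| 150 / 30 | about 0.55–0.61 | about 14–66% |

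Closed-form check for independent markers, P = 1 − (1 − p)^K:
- 100/20: z = 0.10/0.0725 = 1.38, p = 0.084. K = 21 gives 84%; K = 5 gives 36%.
- 150/30: z = 0.10/0.0591 = 1.69, p = 0.045. K = 21 gives 62%; K = 5 gives 21%.

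A longer simulation (8,000 replicates per setting) gives 0.56–0.64 and 26–84% at 100/20, and 0.55–0.61 and 16–63% at 150/30. The table's end points are thus good to a few percentage points.

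**Step 3: would the 95% intervals of Section 7.1 protect, if they were applied?** Not unadjusted. The chance that at least one useless independent marker has its lower limit above 0.5 is 1 − 0.975^K: 12% for K = 5, 41% for K = 21, and 80% for 21 markers in three injury types (K = 63). In simulation, with subgroup sizes of 75 to 500 and a rarer class of 10% to 50%, the winner's interval lay wholly above 0.5 in about 20–49% of null cases with 21 markers and about 8–14% with 5.

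**Step 4: does cross-validation remove the bias?** Only if selection is inside it. For 21 independent null markers, a 20% rarer class and 5-fold cross-validation, the winner's mean AUROC is:

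| N | Selected and reported on the same folds | Selection nested in the training folds |
|---|---|---|
| 500 | 0.57 | 0.50 |
| 167 (one third of 500) | 0.62 | 0.49 |
| 75 | 0.69 | 0.51 |

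**The case against.** The strongest reply is that one loose sentence in a subgroup section is being made to carry the whole study. Much of that reply stands, and it rules out several stronger readings.

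- *A reader might infer that all qualification in this study is by rank.* The documents do not support that. The sentence sits in Section 7.4 only, and the main analysis is set up as a comparison with ALT and total bilirubin.
- *A reader might infer that selection and assessment share a single cross-validation, so the reported AUROCs will be inflated.* Nested cross-validation also uses all the data and both selects and assesses. The wording does not exclude it, and the SAP may specify it. Inflation is a risk left open, not an established fault.
- *A reader might take Section 7.1 to mean that combinations which fail will go unreported.* The sentence is loosely worded, since outperformance is known only after investigation. It does not say that results will be withheld, and Section 2.2 makes the best combination an objective for the listed secondary outcomes.
- *A reader might call false qualification certain.* It is certain only if every marker is useless in that injury type.
- *A reader might quote an expected highest AUROC of 0.66, exceeding 0.60 in 98% of cases, at 100/20.* That requires 21 independent markers, each with its direction chosen from the data. It is the upper extreme, and fewer than 21 may be assayed.

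Deferral to the SAP does not rescue the rule itself. The protocol states who will be qualified, so a SAP that added a bar would have to override it. If the standard markers are ranked in the same list, a new marker could still be qualified on a trivial lead in point estimate.

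**Conclusion.** The rule in Section 7.4 is wrong as written. It declares a good predictor in each injury type with probability 1, without reference to chance or to the standard markers, contrary to the aim in Sections 1.6 and 2.1. That conclusion rests on the text alone.

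The size of the chance advantage rests on assumed subgroup sizes, event shares, marker number and correlation, and should be quoted only as the ranges shown. They are wide, but even with 5 correlated markers the best useless one averages about 0.56 at 100/20 and 0.55 at 150/30.

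The cross-validation wording in Sections 1.6.3 and 7 needs clarification; it is not shown to be in error. Because the rule is confined to subgroups of an observational study, this should be fixed, but it does not undermine the main comparison.

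**What to change.** 1. **Section 7.4.** Replace the ranking with a prespecified criterion. For example, a marker is qualified for an injury type only if the lower confidence bound of its paired AUROC gain over ALT and total bilirubin in that subgroup exceeds 0, adjusted for multiplicity over the markers assayed and the three injury types. Otherwise describe it as highest-ranked and exploratory. Other criteria would serve if they include a bound, a comparator and multiplicity control.
2. **Sections 1.6.3 and 7.** State that marker selection, combination building and threshold choice take place inside the training folds, and that performance is reported from the outer folds only.
3. **Section 7.1.** Reword so that every combination evaluated is reported, whatever the result.

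The cost is analysis effort; no further patients or samples are needed. The downside is that reported AUROCs will be lower and fewer markers will qualify. In a small injury-type subgroup possibly none will, and the exploratory label would then be the accurate description.
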